### Outcomes

#### Clinical outcomes

These refer to physical disability commonly assessed with the EDSS^33^ and other parameters, such as activity and progression, as defined in the 2013 Lublin clinical classification.^34^ Clinical evaluations will be completed with more specific measures of physical and cognitive disability:

Relapses defined as the occurrence, recurrence or worsening of symptoms of neurological dysfunction lasting>24 hour and usually ending with remission, partial or complete. Symptoms occurring within 1 month are considered part of the same relapse.Progression defined as the steady worsening of neurological symptoms and signs for at least 6 months, whether superimposed with relapses or not,^35^ including relapse activity worsening.

Disability is defined as irreversible when the assignment to a given score has been reached and persists for at least 6 months, excluding any transient worsening of disability related to relapses.^36^

#### MRI outcomes

These data represent surrogate markers of disease activity and progression. MRI annual acquisitions will conform to OFSEP recommendations for MRI standardised acquisitions in France.^27 28^ Because raw acquisitions will be available (3D FLAIR, 3D T1, diffusion images), many MRI measures will be assessable, in particular:

T2/FLAIR image lesion load and identification of new lesions compared with previous MRI acquisitions, with measurement of their volume and number.Brain volume and atrophy using T1 images.

#### Patient-reported outcomes

These include the following questionnaires:

Health-related QoL measured with the Medical Outcomes Study 12-items Short Form (SF-12), a self-reporting questionnaire based on the generic QoL SF-36 questionnaire.^37^ The SF-12 was scored with item response theory weights (RAND-12 HSI) that provide physical, mental and global scores.^38^The MusiQoL questionnaire related to specific MS characteristics.^39^Self-perceived health states with the EQ-5D 5L. These health states are associated with utility weights that can be used in an econometric approach.^40 41^Social consequences assessed by employment situation, sick leave occurrence and duration, unemployment or dependency. Employment situation will be declared by patients with MS at annual visits.

#### Combined outcomes

By considering both clinical and MRI data, combined outcomes allow for stratifying patients into active and progressive groups as defined by the last Lublin classification,^34^ in activity defined on clinical and/or MRI features and progression on clinical features only:

No evidence of disease activity (NEDA) is a composite of measures related to disease activity and progression. It is derived from the post hoc analyses of contemporary phase 3 clinical trials of, for example, natalizumab and cladribine.^42^,^44^The Rio score^45^ and the modified Rio score^46^ combine new T2 image lesions and relapses.Progression independent of relapse activity will be also considered.^10^

#### Potential prognostic factors

Factors with a potential prognostic value will be studied in two different sets. First, specific attention will be paid to sociodemographic and clinical determinants and biomarkers of the progression of disability. Such characteristics include age, sex, level of education, occupation, residency, initial relapse, clinical MS form (primary progressive, relapsing remitting and secondary progressive), past and current disease activity, DMTs and comorbidities including health behaviours (smoking, alcohol, body mass index, etc). Comorbidities are assessed using the Functional Comorbidity Index^47^ and the Charlson Comorbidity Index adapted for claims databases.^48^ To enrich prognostic models with potential predictors of disease evolution, questionnaires will be annually proposed.

Second, high efficacy classes of DMT and switches as well as off-label prescriptions are available since disease onset. Nine DMTs are currently available for relapsing remitting MS and secondary progressive MS with activity. These drugs include interferons, glatiramer acetate, teriflunomide, sphingosine 1-phosphate receptor modulators, fumarates, cladribine and five types of monoclonal antibodies.^8 49^

#### Findings to date

A cohort of 2842 individuals has been recruited from July 2018 to September 2020. Their characteristics are described in online supplemental table S1). They are 73.4% women, with mean (SD) age at inclusion 42.7 (11.6) years. Their mean age at onset was 31.7 (10.2) years and median disease duration was 8.8 (4.3–15.7) years. At inclusion, the mean EDSS was 2.4 (1.9) and the course of MS was a unique episode in 14.4%, relapsing remitting in 67.7%, secondary progressive in 11.9% and primary progressive in 6.0%. The mean annual relapse rate was 0.98 (0.80–1.19). The disease-modifying treatment received was highly effective therapy in 50.3%, moderately effective therapy in 30.7%, while 6.4% were naive of DMT and 12.5% had no current treatment. Landmarks at inclusion were documented by an MS diagnosis for less than 6 months in 4.4%, MS progression in the past 12 months in 1.2%, relapse or MRI activity in the past 3 months in 25,5% (with 369 missing values) and remission (NEDA 3) in the past 5 years in 10.7% (with 34 missing values).

We compared the characteristics of 2847 included and 16 239 non-included individuals among 19 806 eligible MS individuals, according to inclusion criteria, attending the 25 centres over the period. The data are presented in online supplemental table S2 and show that among eligible MS individuals, those included have less MRI activity in the past 3 months, an MS diagnosis for more than 6 months, a moderate EDSS and receive more highly effective therapy, with a significant heterogeneity of recruitment across MS centres.

A comparison of their characteristics at inclusion showed that individuals with missing data on clinical outcomes (22.4%), PROs (13.5%) and landmarks (19.2%) were older, with MS onset or MS diagnosed at older age, had slightly lower education, more progressive phenotype, higher EDSS score, and received less active treatment than those without missing data (online supplemental tables S3–S5).

### Future plans

The study participants will be followed until 8 December 2026.

#### Statistical analysis strategy

Several prognostic models will be developed and validated. The model development will be based on a training cohort consisting of a random selection of two-thirds of the centres. The above list of prognostic factors (ie, first, sociodemographic, clinical, imaging, biological variables and comorbidities and second, treatments and the four landmarks) will be considered as three blocks. The prognostic factors will be considered to achieve dynamic predictions^50^ of the following times to events: reaching irreversible EDSS scores of 4, 6 and 7; first relapse; disease progression; MRI outcomes; PROs (QoL), social consequences and combined outcomes of clinical and MRI data reflecting activity and disease progression.

To consider the longitudinal predictors up to the landmark time, we will adapt the methodology proposed by Devaux *et al*.^51^

According to data from the remaining one-third of centres in the external validation cohort, we will use several metrics to appraise the predictive capacities of the models. We will randomise centres and not individuals for learning and validation, because the latter strategy would have been considered as internal validation, questioning the generalisation of the results.^52^

In a stratified medicine perspective, we aim to develop stratified algorithms for medical decision-making for maximising the number of years without disease progression and with the best QoL, this last dimension depending on both the disease activity and the treatment adverse events. The knowledge gained will allow for a clear picture of the history of MS in the 2010–2020s and the various determinants of outcomes. This landmark approach will identify some prognostic factors that play a permanent role and others to be considered at some stages of the disease course for more appropriate decision-making for care, regardless of treatment. We will study the potential of the new classification of disease activity and progression to modify the prognostic classification of cases initially developed using the classical progressive relapse secondary progressive classification.

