## Cohort description

### Study design

#### The OFSEP-HD cohort

The OFSEP-HD cohort is nested in the OFSEP cohort. Patient enrolment started on 10 July 2018 and ended on 11 September 2020 in 25 French MS centres. Individuals were eligible if they had (1) a diagnosis of MS according to the most recent criteria at entry into the HD cohort,^24^ (2) were ≥15 years old at inclusion, (3) had an MS diagnosis after the study start or, if MS onset occurred before the study start, had at least one visit every 2 years after follow-up in an MS centre with prospective OFSEP data collection; (4) had an irreversible Expanded Disability Status Scale (EDSS) score ≤7.0 (permanent use of a wheelchair) at inclusion in the study and (5) signed a written consent form. The criterion 3 for MS onset date allowed for mixing incident and prevalent cases, accelerating recruitment while benefiting from quality data collected during the OFSEP cohort follow-up, extending the possibility to fund the follow-up of included patients over time and increasing the probability to observe landmarks. Non-inclusion criteria were an inability to answer questionnaires and pregnancy at the time of inclusion (figure 1).

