**Figure 1 F1:**
[figure not shown]
OFSEP-HD cohort recruitment flow diagram. HD, high definition; MS, multiple sclerosis; OFSEP, Observatoire Français de la Sclérose en Plaques.

With a sample size of 2842 patients, a factor with a HR of 1.2 could be detected if the event rate was 30%, and one with a HR of 1.6 could be detected if the event rate was 5% (power=0.8; α risk=0.05; SD=0.5).^25^ We acknowledge that our power calculation does not account for multiple testing, as do other cohorts with many exploratory objectives.

This protocol is registered at ClinicalTrials.gov: NCT03603457.

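### The hold-out of a random third of the centres is a centre-level split-sample validation, not an external one, and it takes about a third of the patients out of model development

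*Protocol article*

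**What the plan says.** The Statistical analysis strategy section bases development on "a training cohort consisting of a random selection of two-thirds of the centres". Performance is then assessed "According to data from the remaining one-third of centres in the external validation cohort", by several metrics that are not named. The reason for splitting by centre is given: "We will randomise centres and not individuals for learning and validation, because the latter strategy would have been considered as internal validation". The section adds that a split by individual would put the generalisation of the results in doubt. It mentions neither repetition of the split nor a final refit on all centres.

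Enrolment "ended on 11 September 2020 in 25 French MS centres". The article describes one set of eligibility criteria and one enrolment window for all of them, a standardised form, one clinical database software, common MRI acquisition recommendations and one annual visit schedule (The OFSEP-HD cohort, The OFSEP cohort, Multisource data collection).

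The power statement below Figure 1 uses the whole cohort: "With a sample size of 2842 patients, a factor with a HR of 1.2 could be detected if the event rate was 30" per cent, and "one with a HR of 1.6 could be detected if the event rate was 5" per cent ("power=0.8; α risk=0.05; SD=0.5").

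**The concern.** Two things are at stake.

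- **The label.** External validation is normally understood as a test in data that arose separately from the development data: another place, period or system of collection. Here chance alone decides which centres are held out, so the two groups are exchangeable by construction. Good performance would show that the model reproduces in other centres of the same network. That is worth knowing, but it is weaker than what the label conveys. The Introduction motivates the work by the insufficient validation of 75 earlier models, so the strength of the validation claim matters.
- **The use of the data.** A fixed hold-out takes about a third of the events away from model-building and leaves performance to be estimated in the other third alone. The prognostic tools are a main product of the cohort, and both halves of the task are weakened.

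**Working it through.** **Inputs from the article.** N = 2842; 25 centres; two-thirds for development; event rates 30% and 5%; power 0.80; alpha 0.05; SD of the factor 0.5. Sidedness is not stated, and two-sided is assumed.

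**Step 1: reproduce the stated figures.** For one factor in a Cox model, with D events,

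detectable HR = exp[(1.960 + 0.842) / (0.5 × √D)].

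- 30%: D = 2842 × 0.30 = 852.6; HR = exp(2.802 / 14.60) = 1.21 (stated 1.2).
- 5%: D = 2842 × 0.05 = 142.1; HR = exp(2.802 / 5.96) = 1.60 (stated 1.6).

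The second figure is reproduced exactly and the first after rounding to one decimal. Power is 76% at exactly HR 1.2 and 80% at HR 1.6.

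**Step 2: the development part.** On average 2842 × 2/3 ≈ 1895 patients.

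| Event rate | Events, all centres | Events, development | Detectable HR, all | Detectable HR, development | Power for the stated HR in development |
|---|---|---|---|---|---|
| 30% | 853 | 568 | 1.21 | 1.26 | 58% (HR 1.2) |
| 5% | 142 | 95 | 1.60 | 1.78 | 63% (HR 1.6) |

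Two-thirds of 25 is not a whole number. With 17 or 16 development centres of equal size the detectable HR is 1.26 to 1.27 at 30% and 1.77 to 1.80 at 5%.

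**Step 3: the validation part.** On average 2842 − 1895 = 947 patients in 8 or 9 centres, with 284 events at 30% and 47 at 5%. Suppose a true AUC of 0.70 (assumption; Hanley-McNeil formula, binary outcome, no censoring, no centre effect):

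- 5% events: standard error 0.043, so the 95% interval is 0.70 ± 1.96 × 0.043, about ± 0.085. If all 2842 patients contributed, the standard error would be 0.025.
- 30% events: standard error 0.019, against 0.011.

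**Step 4: dependence on the draw.** Suppose a centre's log calibration ratio (observed to expected) varies with SD τ between centres of equal size. The mean over 8 held-out centres then differs from the mean over the 17 others with SD τ × √(1/8 + 1/17) = 0.43τ, through the draw alone. For τ = 0.1, 0.2 and 0.3 (assumptions) this is 0.04, 0.09 and 0.13 on the log scale.

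The size of the hold-out depends on the draw as well. Centre sizes are not given. If they were lognormal, 8 random centres would hold these shares of the cohort in 95% of simulated draws:

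- coefficient of variation 0.5: 24 to 42%
- coefficient of variation 0.75: 20 to 47%
- coefficient of variation 1.0: 17 to 51%

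These coefficients are assumptions, so the ranges illustrate the problem and do not estimate it for this cohort.

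**The case against.** The best case for the plan is that the label should be read against the claim. The Economic analysis plan section limits the expected impact to ambulatory patients in French expert centres. Unseen French MS centres are that setting, and the procedure stands beside the label, so nobody is misled about what was done. The first part stands: holding out whole centres does test the setting that is claimed. It does not make the held-out centres external, because they come from the same cohort and were picked by chance.

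It can also be said that a one-factor test is an indirect measure of the stability of a multivariable dynamic model, and that the search for determinants is a separate objective that the article does not confine to the training centres. Both are fair. The hazard ratios measure the information lost to development. They do not show that the power statement for the whole cohort is wrong.

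Four stronger readings are tempting, and the article does not support them:

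- *The centres are shown to be very unequal.* The reported finding, "with a significant heterogeneity of recruitment across MS centres", comes from comparing included with non-included eligible patients. It gives no centre sizes, outcome rates or model performance.
- *The split is certainly done once, and a third of the data is thrown away.* The article mentions no repetition or refit, but does not exclude them, and the held-out third is used for validation.
- *The hold-out cannot show variation between centres.* Eight or nine intact centres can show some, imprecisely.
- *The diagnosis landmark will be validated in about 42 patients.* That is a third of the 125 (4.4%) who were within 6 months of diagnosis at inclusion. The landmark is the visit at which the diagnosis is made, and the cohort includes prevalent cases with earlier OFSEP data, so 125 is not shown to be the analysis set.

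**Conclusion.** The concern holds in this form: the plan describes a centre-level split-sample validation and gives it the name of an external one. That conclusion rests on the article's text and needs no assumption about numbers.

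The cost to development is moderate for frequent outcomes and larger for rare ones: about 285 of 853 events at 30% and 47 of 142 at 5% are unavailable for model-building. These are averages, since the plan reserves a third of the centres and not a third of the patients. The cost to validation is clearest for rare outcomes, where about 47 events in 8 or 9 centres give a wide interval and only a weak picture of variation between centres. How uneven the split may turn out is unknown without the centre sizes.

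The choice is defensible as a first design, but a better one is available from the same data. It should be changed before the models are built.

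**What to change.** 1. Use internal-external cross-validation by centre. Hold out each centre in turn and repeat the whole model-building, including variable selection, in the others. Where a centre has too few events for an outcome or landmark, hold out groups of centres. The average centre has 2842 / 25 ≈ 114 patients, hence about 34 events at 30% but fewer than 6 at 5%. Five centres together have about 568 patients and 28 events at 5%.
2. Report pooled discrimination and calibration with their heterogeneity. Give a prediction interval for a new centre only where single centres are the held-out unit. Groups of five do not directly provide one.
3. Fit the final model on all 25 centres.
4. Call the procedure internal-external validation, and keep the word external for data from outside the cohort.

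This needs no new data and keeps the sound idea of holding out whole centres. It costs computation, which is not trivial with many outcomes at four landmarks, and model-building must be scripted so that it can be repeated. There would no longer be a single frozen hold-out set.

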#### Economic analysis plan

Two types of economic analysis will be conducted: (1) a cost-of-illness analysis for identifying the current cost burden to society, together with the identification of the main cost drivers and (2) a cost-effectiveness analysis for exploring the efficiency of recent DMT treatments, namely biotherapies, compared with standard treatments. The effectiveness of new treatments for previously defined outcomes will be assessed after controlling for the prognostic information determined above.

We expect the findings of this research from the OFSEP-HD cohort to have an impact on MS diagnosed adult, with limited disability progression and preserved ambulatory ability, whatever the disease duration, potentially eligible to DMT, and followed in a French expert centre, so representing a large proportion of French MS ambulatory people.

#### Collaboration

Scientific collaboration based on data sharing with other teams in the scientific community will be open and encouraged, in line with the funding body policy. Any scientific project will be examined by the OFSEP scientific committee, also in consideration of technical feasibility and full respect of general data protection rules.

### Patient and public involvement

Patient associations are already involved in different ways in the OFSEP project. To include patient representatives more formally in the governance of OFSEP, one patient representative from UNISEP, the national federation of MS patient associations, has joined the Steering Committee, with a voting right. Patients were not involved in the OFSEP-HD study research question or design.

### Ethics and dissemination

In accordance with French laws, ethical approval was obtained by a national institutional review board (ethical approval received on 15 June 2018 from the Comité de Protection des Personnes Sud-Ouest et Outre-Mer IV (no. CPP18-036a/2018-A00882-53)). Dissemination of the OFSEP purpose and objectives and dissemination of results will involve different directions and publics.

The international scientific community through papers in peer-reviewed journals and abstracts in conferences.The French neurological community and participants of the OFSEP cohort.Patients and the public: this will be a good opportunity to give concrete examples of the impact of research, with direct impact on the management of patients. The involvement of a patient representative will allow for a better understanding of patient expectations and needs.

## Data Availability

Data are available upon reasonable request.
